#### Secondary outcomes

Fisher’s exact test will be used to compare the groups regarding 1) the informed choice regarding statin treatment, smoking, blood pressure and HbA1c; 2) rates of individual goal achievement (yes/no): statin choice, smoking status; and 3) rates of changed treatment goals.

Unpaired t-tests will be used to compare the study groups regarding 1) the average difference between planned and achieved values of blood pressure; 2) the average difference between planned and achieved level of HbA1c; and 3) the level of realistic expectations and knowledge.

Mann–Whitney *U*-test will be used to compare the medication prescription from T0 to T2, T3 (increase/unchanged/decrease).

Unpaired t-tests will be used to compare the study groups regarding 1) the change of clinical parameters (HbA1c, blood pressure, cholesterol) from T0 to T3 and 2) the mean difference between perceived risk and assessed risk between groups.

Difference in the chosen prioritised treatment goals between groups will be compared by using chi-square test.

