## Objectives

The key hypothesis is that patients who actively participate in decision making show better adherence to their individual treatment goals. We primarily investigate if patients allocated to the ISDM group are more likely to adhere to their antihypertensive or statin medication. We also investigate if patients in the ISDM group achieve their HbA1c- and blood pressure goals with fewer drug prescriptions and if they achieve lower levels of HbA1c, blood pressure, or cholesterol with unchanged or fewer prescriptions.

We also hypothesise that patients in the ISDM group less frequently prioritise intensified glucose control and more frequently blood pressure control and statin treatment.

Further objectives are to assess if the ISDM group achieves a better understanding and higher levels of realistic expectations regarding heart attack risk and probabilities of benefits and harms of preventive options.

Alongside to the trial, processes and barriers of implementation will be qualitatively assessed. We expect that the implementation of the ISDM programme in primary care will be perceived as feasible. Patients will be perceived as more competent. The workload will not be perceived as more stressful and time consuming.

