### Randomisation and blinding

Randomisation of practices will be performed after patient recruitment and retrieval of baseline data. To ensure close balance of entities in each group, randomisation will be performed in blocks of 4. The randomisation sequence will be generated by the Centre for Clinical Studies at the University Hospital Jena. Blinding of practices that deliver the intervention programme is not feasible. However, they will be asked to keep the allocation blinded as far as possible, i.e. to not reveal study details to the patients. Patients will be informed that the objective of the study is to compare two different approaches to better acknowledge patients’ preferences and values in decision making on preventive measures and that they have an equal chance of receiving the intervention or the control programme. Allocation concealment will be ensured for database entry and statistical analyses.

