Secondary outcome measures are: 1) informed choice regarding statin treatment, blood pressure control, glucose control, and smoking cessation; 2) the achievement of treatment goals regarding statin treatment, blood pressure, HbA1c, and smoking cessation; 3) prioritisation of treatment goals; 4) realistic expectations [59] on the individual heart attack risk and on probabilities of benefits and harms of the available treatment options; 5) the level of patient knowledge and understanding relating to the concept of risk, the notion of heart attack risk, and the benefits and harms of preventive treatment.

Informed choice will be assessed equivalently to the *informed choice* construct developed by Marteau et al. [58]. To determine whether a patient makes an informed (or uninformed) choice, we assess and then combine three constructs: 1) knowledge relating to the concept of risk, the notion of heart attack risk, and the benefits and harms of preventive treatment; 2) the patient’s treatment goal; and 3) adherence to the decision.

Since an operationalization of prioritised goals is not feasible in the context of this study, we assess them separately. A categorisation of blood pressure and HbA1c goals in achieved vs. not achieved is not feasible at the individual level. Defining particular cut-off levels would be arbitrary. The achievement of these goals will be assessed by comparing group differences. Prioritised treatment goals will be described for each study group.

Additional outcome measures are change in clinical parameters (HbA1c, blood pressure, cholesterol) from baseline to follow-up and medication prescriptions. A previous RCT showed that patients who had participated in a structured hypertension self-management programme achieved lower blood pressure levels. At the same time prescription of antihypertensive medication decreased [60], which indicates better adherence to the prescribed medication. In the current cRCT, medication prescription will be interpreted in the light of the achievement of the corresponding treatment goals.

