### Data collection

Patient records and standardised forms will be used to collect baseline characteristics and outcome data. Outcome data is documented electronically as scheduled in the DMP.

Baseline characteristics include age, gender, first-language (usually spoken at home), educational status, body mass index (BMI), smoking status, blood pressure, LDL-cholesterol level, total cholesterol level, HbA1c level, current medication, and previous participation in diabetes and hypertension patient education programmes. Individual baseline risks of myocardial infarction are calculated by using a risk assessment tool. The tool uses age, smoking status, and clinical parameters and is derived from the Framingham function calibrated [61] to the average heart attack risk in the German population.

The treatment goals set by the individual patient in the ISDM group will be assessed after the teaching session and after the consultation by extracting them from the documentation sheet. Treatment goals of the control group will be assessed at a practice visit by using a standardised documentation form.

Telephone interviews will be conducted to assess the adherence to the current drug prescriptions. A standardised interview guide will be developed including questions such as *“Patients with diabetes often need to take several pills. I am interested in your current use of pills. Could you tell me, which medication boxes do you use? Which substances are labelled on the boxes?”*, and “*Have you ever missed any pills in the past seven days?”* [62]*.* Patients are classified as non-adherent if their answers are inconsistent with the prescriptions. Patients without antihypertensive prescription will be asked about statin medication. Patients with neither antihypertensive nor statin prescription will not be included in data analysis for the primary endpoint. In order to avoid socially desirable answers, the interviews will be conducted by a study assistant of the study organising centre, independent from the practices and blinded towards the allocation. Interviews will be audio-taped. In ambiguous cases, the tape will be analysed by a project member who is also blinded toward patients’ allocation. Inter-rater consensus will be achieved by discussion. Cholesterol levels at baseline and follow-up will be used to validate data on adherence to statin choice.

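### Change in HbA1c, blood pressure and cholesterol is tested on raw change scores, which over-correct chance baseline differences and lose some precision, although baseline values exist before randomisation

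*Protocol article*

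**What the plan says.** Under Data synthesis, Secondary outcomes, the protocol article states: "Unpaired t-tests will be used to compare the study groups regarding 1) the change of clinical parameters". The item in full is "the change of clinical parameters (HbA1c, blood pressure, cholesterol) from T0 to T3", that is, between baseline (T0) and six months (T3). An unpaired t-test takes no covariate, so this is a method the article has chosen, not a detail it leaves open.

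The Outcomes section ranks these measures below the five numbered secondary outcomes: "Additional outcome measures are change in clinical parameters (HbA1c, blood pressure, cholesterol) from baseline to follow-up and medication prescriptions". They still serve a stated aim, since Objectives asks of the intervention group "if they achieve lower levels of HbA1c, blood pressure, or cholesterol with unchanged or fewer prescriptions".

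The material for adjustment is available. Data collection lists among the baseline items "smoking status, blood pressure, LDL-cholesterol level, total cholesterol level, HbA1c level, current medication". Randomisation and blinding says: "Randomisation of practices will be performed after patient recruitment and retrieval of baseline data". Data synthesis plans only a descriptive use of baseline characteristics. On balance between arms, the article says: "To ensure close balance of entities in each group, randomisation will be performed in blocks of 4". Sample size gives 24 practices and 306 recruited patients.

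**The concern.** Blocks of 4 even out the number of practices per arm, not the HbA1c, blood pressure or cholesterol of their patients. With 24 practices, some of them diabetes-specialised, moderate baseline differences can arise by chance. An arm that starts higher by chance tends to fall further through regression to the mean, and a change score counts that extra fall as effect.

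At stake is the reading of the objective on equal or lower levels with unchanged or fewer prescriptions. A fall that is partly regression to the mean could look like better control, or could hide it. Precision is also given up although the baseline values are already collected and cannot have been influenced by allocation.

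**Working it through.** **The article's own figures.** It gives no standard deviation, correlation or sample size for these outcomes. Its primary-outcome calculation reproduces: exact Fisher power for 60% against 80% with 90 per group is 0.802 (two-sided 5% assumed); the design effect is 1 + (13 − 1) × 0.03 = 1.36; 90 × 1.36 = 122.4, stated as 122; 244/0.8 = 305, stated as 306.

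**Inputs.** 24 practices and 306 patients, so 153 per arm and 306/24 = 12.75 per practice (Sample size). A 12 to 12 split is inferred from the equal chance of allocation and blocks of 4. The correlation r is an assumption, shown from 0.3 to 0.9. Practice-level ICCs for baseline values are also assumed, from 0 to 0.10.

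**Size of chance imbalance.** In baseline SD units, the SD of the difference between arms is √[(2/153)(1 + 11.75 × ICC)]:

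| ICC | SD of difference | 95% range, ± |
|---|---|---|
| 0 | 0.11 | 0.22 |
| 0.03 | 0.13 | 0.26 |
| 0.10 | 0.17 | 0.33 |

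**Effect on the two estimates, equal variances.** Given a baseline difference D, the change-score contrast is shifted by −(1 − r)D; the adjusted contrast is not. The variance ratio, adjusted to change score, is (1 − r²)/[2(1 − r)] = (1 + r)/2. If the adjusted test has 80% power, the change-score test has power Φ(2.80 × √[(1 + r)/2] − 1.96).

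| r | Variance ratio | Change-score SE larger by | Change-score power | Shift at D = 0.26 SD |
|---|---|---|---|---|
| 0.3 | 0.65 | 24% | 62% | 0.18 SD |
| 0.5 | 0.75 | 15% | 68% | 0.13 SD |
| 0.7 | 0.85 | 8% | 73% | 0.08 SD |
| 0.8 | 0.90 | 5% | 76% | 0.05 SD |
| 0.9 | 0.95 | 3% | 78% | 0.03 SD |

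**Simulation check.** The set-up was 24 practices split 12 to 12, 10 patients each, ICC 0 and 0.03, no true effect and 4,000 repeats.
- The variance ratio was 0.74–0.76 at r = 0.5 and 0.85–0.86 at r = 0.7.
- The change-score estimate moved with the baseline difference with slope about −0.5 and −0.3 respectively; the adjusted estimate had slope about 0.
- Both estimators averaged within 0.003 of zero, so neither is biased over repeated randomisations.

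**Unequal variances.** With k = SD(T0)/SD(T3), the variance ratio becomes (1 − r²)/(1 + k² − 2rk). For k = 0.8, an illustrative value not in the article:
- r = 0.5: 0.75/0.84 = 0.89
- r = 0.7: 0.51/0.52 = 0.98

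Eligibility and recruitment requires HbA1c below 9%, which truncates the baseline distribution but not the follow-up, so k below 1 is plausible for HbA1c.

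**Reported intervals.** The unpaired t-test also ignores practice. If the primary-outcome design effect applied here (an assumption), it would understate the SE by a factor of √1.36 = 1.17. The precision loss from using change scores is a factor of 1.15 at r = 0.5 and 1.08 at r = 0.7.

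**The case against.** The strongest reply is that a change score does deal with baseline, is valid under randomisation, and concerns outcomes that the article itself calls additional. Much of this stands. A reader might infer that imbalance is left uncorrected, or that the planned test is biased. Neither follows: baseline is subtracted in full, and the error exists only conditional on the imbalance that occurs. A typical imbalance is also modest in effect: one SD of it (0.13 at ICC 0.03) shifts the contrast by 0.3 × 0.13 = 0.04 SD at r = 0.7.

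A reader might also quote a saving of 15 to 35% in patients. That needs r between 0.3 and 0.7 and equal variances. The article supplies neither, and the saving is 5 to 10% at r = 0.8–0.9 and 2 to 11% at r = 0.5–0.7 if k were 0.8.

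Nor can it be said that the planned analysis will report wider intervals. By ignoring clustering it understates its SE, which may offset or exceed the loss from using change scores.

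Finally, the argument might seem to extend to the planned-versus-achieved comparisons of blood pressure and HbA1c. It does not: those subtract a goal set after randomisation, not the baseline value, so neither the formula nor the regression-to-the-mean reasoning carries over.

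What the reply does not remove is that the article specifies the weaker of two simple analyses when the covariate is in hand before allocation.

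**Conclusion.** The point holds in limited form, as an improvement that should be made. For T0 to T3 change in HbA1c, blood pressure and cholesterol, the planned test over-corrects chance baseline differences by (1 − r) times their size and has more sampling variance than a baseline-adjusted comparison. The adjusted variance is 0.65 to 0.95 of the change-score variance for r from 0.3 to 0.9. Both statements assume equal variances at T0 and T3. The direction is well established; the size is not, because r and the variances are not given. The primary outcome, the sample size and the main conclusion are untouched.

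**What to change.** For these three outcomes, replace the change-score t-tests with a linear mixed model of the T3 value on arm, with the T0 value of the same measure as covariate and practice as a random effect. Report the adjusted difference with its 95% interval, using degrees of freedom suited to 24 practices. The practice effect is needed because Sample size itself says that patients in the same cluster tend not to be independent; baseline adjustment alone would leave that problem in place. Mean change per arm can still be shown descriptively.

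The cost is a revision of the analysis wording. No further data, visits or patients are required.

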The ISDM programme has been evaluated in a randomised, controlled trial (RCT) [34] under high fidelity conditions in an outpatient setting at the Department for Endocrinology and Metabolic Diseases of the University Hospital Jena, Germany. Follow-up data is currently being collected. Primary endpoint has been patients’ knowledge regarding the individual heart attack risk, benefits and harms of preventive options. Secondary endpoints have been realistic expectations and achievement of treatment goals. Preliminary data assessed after the teaching sessions are available [35]. Patients allocated to the ISDM programme achieved higher scores of knowledge and higher scores of realistic expectations. ISDM patients more often prioritised an achievement of their blood pressure goals. Blood glucose goals were prioritised by 32.9% of the ISDM group and by 60% of the control group. Prescriptions of statins did not change from baseline to post teaching, but individual choice to not taking statins indicated changes of adherence to statin medication.

In sum, the study showed that the ISDM programme has impact on patients’ knowledge and prioritisation. However, it may not realign power-imbalance between patients and their health care team. Hence, the ISDM programme has been augmented by including an additional training module for physicians to facilitate implementation of SDM.

The aim of the planned cluster randomised, controlled trial is to evaluate the efficacy of the ISDM programme in the primary care context. Alongside to this trial, the implementation process will be evaluated using qualitative research methods.

The reporting of this study follows current statements [36,37].

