**Table 2 Tab2:** **Data collection**

**Outcomes**	**Measures**	**Follow-up**
Adherence to antihypertensive or statin therapy	Prescription of antihypertensive drugs and statins (patient record)	T3
	Intake of antihypertensive medication or statins (structured telephone interview)	T3
Informed choice	Knowledge	T1
	Treatment goals: Statin choice, levels of blood pressure and HbA1c, and smoking	T1
	Achievement of goals regarding statins, blood pressure, HbA1c, and smoking	T3
Achievement of goals	Treatment goals: Statin choice, levels of blood pressure and HbA1c, and smoking as well as patient’s prioritised treatment goal (patient record)	T2
	Statin intake (structured telephone interview)	T3
	Blood pressure (standardised measure)	T3
	HbA1c level (laboratory value)	T3
	Smoking cessation (structured telephone interview)	T3
Prioritisation	Prioritised treatment goal: Statin choice, blood pressure, HbA1c or smoking cessation	T1, T2
Realistic expectations	Questionnaire developed based on the contents of the DA and the teaching module	T1
Knowledge	Questionnaire developed on the basis of Bloom’s taxonomy [65] and evidence-based information on heart attack prevention in type 2 diabetes [33]	T1

T1 = at the end of the teaching session; T2 = during physician consultation; T3 = at 6 months follow-up.

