### Sample size

We hypothesise patients in the ISDM group to reach higher adherence to prescriptions of antihypertensive and statin medication.

Based on current DMP-data [39] and the preliminary results of the pilot RCT [35], we assume that approx. 60% of patients in the control group will adhere to the choice. We estimate that more than 80% of patients in the intervention group will adhere.

We calculate the sample size providing 80% power to detect an absolute difference of 20% between the intervention and the control group, using Fisher’s exact test at the 5% level of significance. Thus, in a non-cluster RCT data on about 90 patients per group (180 participants) would need to be included in data analysis.

Since observations on individuals in the same cluster tend to be non-independent, the effective sample size is less than the total number of individual participants. The reduction in effective sample size depends on the average cluster size (m) and the degree of correlation within clusters (intracluster correlation coefficient, ICC). To retain power, the sample size should be multiplied by the so-called design effect (DE = 1 + (m - 1) × ICC) [36]. However, we did not identify data, allowing an estimation of a probable ICC for the primary endpoint used in our study. Krones et al. [28] reported an ICC of 0.06 for an endpoint relating to patient participation. Branda et al. [63] published an ICC of 0 or nearly 0 for knowledge, decisional comfort, and medication adherence. Thus estimating an ICC of 0.03 and a mean cluster size of 13 participants, we calculate with a design-effect of DE = 1.36. Hence, data on 122 patients per study arm (total 244 participants) need to be included in data analysis. Estimating a drop-out rate of about 20%, 306 participants will be recruited for randomisation, distributed across 24 clusters (practices). This power calculation was conducted by [name] Biostatistician (Jena, Germany).

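### The single chi-square test planned for the prioritised goal does not by itself test the Objectives' hypothesis about glucose control, blood pressure and statins

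*Protocol article*

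**What the plan says.** The Objectives of the protocol article give prioritisation its own directional hypothesis, namely that "patients in the ISDM group less frequently prioritise intensified glucose control and more frequently blood pressure control and statin treatment". Smoking cessation is not part of it.

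The Outcomes section lists prioritisation of treatment goals as the third secondary outcome and adds: "Prioritised treatment goals will be described for each study group". Table 2 defines the variable as "Prioritised treatment goal: Statin choice, blood pressure, HbA1c or smoking cessation" and schedules it at two time points, where "T1 = at the end of the teaching session; T2 = during physician consultation".

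Under Secondary outcomes in the Data synthesis section, the inference is one sentence: "Difference in the chosen prioritised treatment goals between groups will be compared by using chi-square test". It gives no table layout, contrast or time point.

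The Background reports the pilot trial as a comparison of one category: "Blood glucose goals were prioritised by 32.9% of the ISDM group and by 60% of the control group".

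**The concern.** A chi-square test over four categories has the null hypothesis that all four shares are equal in the two arms. The Objectives ask something narrower: is the glucose share lower, and are the blood pressure and statin shares higher? Rejecting the broad null does not establish the narrow claim. Priorities could move from blood pressure to smoking cessation, or from blood pressure to statins, with no change in glucose control, and the test could still be significant.

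A shift towards smoking cessation is possible in this trial, because the teaching session also supports patients in setting a smoking goal (Intervention group section). What is at stake is how the result is read. After a significant p-value, the authors would have to decide post hoc which cells produced it, although the question had been stated in advance and the pilot had already been reported as a glucose comparison.

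**Working it through.** **Inputs from the protocol**
- Pilot glucose priority: 60% control, 32.9% intervention (Background).
- Four categories (Table 2), so a two-by-four table has (2 − 1) × (4 − 1) = 3 degrees of freedom.
- Analysed size 122 per arm, ICC 0.03, mean cluster size 13 (Sample size).

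**Assumptions**
- The protocol does not say how the 40% of control patients who do not prioritise glucose divide. Base assumption: blood pressure 20%, statin 10%, smoking 10%.
- Two-sided 5% level; patients treated as independent. Effective size 122 / 1.36 ≈ 90 per arm is a rough allowance for clustering; the ICC was not estimated for this outcome.

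**The protocol's own figure.** The only sample size given is for the primary outcome, with "80% power to detect an absolute difference of 20% between the intervention and the control group, using Fisher’s exact test at the 5% level". Enumerated power of the two-sided Fisher test at 60% versus 80% with 90 per arm is 0.802. The design effect is 1 + 12 × 0.03 = 1.36, and 90 × 1.36 = 122.4. With 20% drop-out, 122 / 0.8 = 152.5, so 153 per arm and 306 in total. The stated figures reproduce. No power is stated for prioritisation.

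**Formula.** With shares c and t in the control and intervention arms and their mean m = (c + t)/2 in each category, the noncentrality is λ = n × Σ[(c − m)² + (t − m)²]/m. Power is the probability that a noncentral chi-square exceeds 7.815 (3 df) or 3.841 (1 df).

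**Glucose unchanged at 60%** (order: glucose / blood pressure / statin / smoking; control 60/20/10/10)
- Intervention 60/10/10/20. The categories that move are blood pressure (m = 0.15) and smoking (m = 0.15): λ = 122 × (0.005/0.15 + 0.005/0.15) = 8.13; rejection 66%.
- Intervention 60/15/5/20: λ = 122 × (0.00125/0.175 + 0.00125/0.075 + 0.005/0.15) = 6.97; rejection 59%.
- Intervention 60/10/20/10 (blood pressure to statin only): λ = 8.13; rejection 66%.
- In all three the glucose-versus-other test has λ = 0 and rejects in 5%.
- At 90 per arm the three figures are 52%, 45% and 52%.

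Simulation (20,000 trials per scenario) gives 67%, 59% and 67% at 122 per arm.

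**Glucose falls as hypothesised**, the shift going 2:1 to blood pressure and statin, 122 per arm:

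| Glucose, control to intervention | Four-category test | Glucose versus other |
|---|---|---|
| 60% to 32.9% (pilot) | 97.5% | 98.9% |
| 60% to 40% | 80.3% | 87.8% |
| 60% to 45% | 53.8% | 65.0% |
| 60% to 50% | 26.2% | 34.8% |

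If statin priority is rare in control (60/28/2/10 moving to 45/33/12/10), the order reverses: 83.4% for the four-category test, 65.0% for the glucose test. Over 20,000 random control splits with a 15-point shift, the four-category test was the weaker in only 48%.

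**Glucose rises from 60% to 75%** (intervention 75/10/5/10): the four-category test rejects in 66%, the two-sided glucose test in 71%.

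**The case against.** The strongest reply is that the secondary outcome is defined neutrally, as prioritisation over four goals. If priorities move to smoking cessation, prioritisation really does differ, and the chi-square test is right to say so. That stands: such a rejection is not a false positive for the outcome as defined. It still does not support the narrower hypothesis in the Objectives.

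Second, the four-category layout is inferred. The article does not state it, separate two-by-two tests are not excluded, and follow-up contrasts are often left to a statistical analysis plan. This limits the weight of the point. But the article itself states both the hypothesis and a single test, and on the natural reading they do not match.

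Third, the planned description by group will show where and in which direction the goals moved. It will, but without a pre-specified contrast any inference about the glucose share remains post hoc.

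A reader might go further and infer two things that the protocol does not support. One is that the chi-square test is defective because it can reject when patients move towards glucose control. Any two-sided test does that; the glucose comparison does so slightly more often (71% against 66%), and the described percentages will show the direction. The other is that the chi-square test loses power for the hypothesised shift. That depends on a control split the protocol does not give; the loss is about 1 point at the pilot effect and can become a gain.

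Finally, the 59% to 66% rests on an assumed doubling of smoking priority from 10% to 20%. Nothing in the protocol predicts such a shift. The figure shows what the test responds to; it is not a forecast.

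**Conclusion.** The mismatch holds, as a minor point. On the natural reading, the only p-value planned for prioritisation tests equality of four shares, whereas the Objectives state a hypothesis about three named goals. A significant result would therefore not by itself confirm that hypothesis: with the glucose share unchanged, rejection is about 59% to 66% at 122 per arm (45% to 52% at an effective 90) for a 10-point smoking gain. These figures depend on the assumed 60/20/10/10 control split and on one test over all four categories. Neither the direction of rejection nor a general loss of power is a ground for the point.

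**What to change.** State in the Secondary outcomes analysis that the test of the prioritisation hypothesis is the between-arm difference in the proportion prioritising HbA1c versus any other goal, at one named time point (T1 or T2). Give it a confidence interval that allows for clustering by practice; the tests now listed state no such allowance, so the method has to be named.

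Report the blood pressure and statin proportions beside it as between-arm differences with confidence intervals. They are needed because a lower glucose share could be taken up by smoking cessation alone, which would support only half of the hypothesis. Do not require all three differences to be significant: with 60/20/10/10 moving to 45/30/15/10 at 122 unclustered patients per arm, simulation puts glucose and blood pressure both significant in about 38% of trials and all three in about 7%.

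Keep the four-category table, with its chi-square test if wanted, as supportive description.

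The change is to wording and analysis only; it needs no new data, visits or patients. The downside is that a shift confined to smoking cessation would be described and would not be the main test.
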